## 6.9 Analytical Plan

### 6.9.1 Analysis of clinician focus groups and interviews and patient/family caregiver interviews

All focus group data and interview data will be recorded digitally, transcribed verbatim, and analyzed on an ongoing basis using interpretive description. To ensure trustworthiness and rigor, we will employ iterative cycles of engagement with users (credibility), generate an audit trail (confirmability), and detailed

reporting of the context (transferability)). The transcripts from the first focus group will be read and re-read by 3 researchers to generate an initial codebook (shaped to answer the research objectives) and to encourage interrater reliability. The codebook will be refined in an iterative fashion throughout the analysis. Codes will be categorized and, with evolving analysis, themed. In addition, data about QPSS usage will be monitored and tabulated and used to inform the analysis for qualitative data, with the goal to better understand usages of different aspects of the QPSS for care planning and shared decision making. We will store and code all qualitative data into NVivo.

## 6.9.2 Analysis of outcomes data

### 6.9.2.1 *Sample size justification*

For purposes of estimation, if we assume the effect of routine use of the QPSS intervention is equivalent to changing an average day into a good day for patients (based on the MQOL). Our power analysis has shown that sample sizes of 432 and 158 would be needed to detect small to moderate effect sizes. We propose a larger sample of 540 (180 for each group) for both patients and family caregivers to account for attrition and a small to moderate effect. Accordingly, each group (pre-intervention, control, intervention) will consist of a total of 180 patients and 180 family caregivers.

Quantitative data will be analyzed using descriptive statistics to describe the pre-intervention comparator sample for patients and family caregivers. Comparative analyses will be completed as part of stage 2 of the project. Following standard descriptive statistical analyses, the effect of the intervention will be assessed based on an intention to treat analysis, as recommended by CONSORT. All tests will be two-tailed with an alpha level of 0.05. The analysis will focus on the comparison of trajectories of the outcome measures across the randomized treatment and usual care groups stratified by home care office. The area under the curve (AUC) will be calculated for each trajectory (up to six times of administration per participant) to create a summary score. This robust approach is recommended when the goal is to arrive at an overall summary measure over a period of time and when unsystematic fluctuations between measurement points are anticipated (which are not readily captured by fitting a model-based trajectory). Analysis of covariance will be used as the primary method of analysis to compare AUC scores of both outcomes (QOL and health care experience) across the intervention and control groups while controlling for within- and between-group differences (clustered by home care office). A limitation of this approach is that the shapes of the trajectories are not taken into account. We will therefore supplement the primary analysis using (a) graphical displays to visualize the trajectories and (b) individual growth modeling to ascertain whether characteristics of the shapes of the trajectories (slope and curvatures) are different for the three groups. Differential item functioning analyses will be conducted on the outcome measures to examine potential gender bias in measurement. Additionally, biological sex will be included as a moderator in the hypothesis testing. Descriptive statistics will be used to describe the use of interventions by clinicians to address identified areas of patient and family caregiver needs.

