### 6.3.4 Allocation to intervention and control conditions

Consenting patients at each home care office will be randomly assigned on a 1-to-1 basis to the intervention or usual care group using a computerized random number generator. Randomization will be stratified by site. To ensure that both members of patient-family caregiver dyad are assigned to the same group, consenting patients will be randomized (whether or not they intend to provide outcome data) and if they have a participating family caregiver, the caregiver will be assigned to the same group. [name], co-PI, is in Montreal and completely removed from the recruitment and allocation process. She will generate and download the randomization sequence, place group allocation on a folded paper inside sequentially numbered opaque envelopes for each site, and mail all envelopes to [name]. She will store a copy of the randomization sequence in a locked filing cabinet in a locked office in Montreal.

The research assistant will inform the research coordinator as soon as a patient (and family caregiver if applicable) is recruited. The coordinator will open the next sequentially numbered allocation envelope to reveal group assignment. She will immediately inform the clinicians in the respective home care office of any patients/family caregivers allocated to the intervention group via generic email notification.

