#### 6.4.2.5 *Stage 2*

For the RCT, we will recruit a total of 360 patients and 360 family caregivers across all sites (see [Appendix 4](#)). The number of participants at each site will vary depending on the size of the site. The RCT participants may include Stage 1 participants, but will not include individuals who have used the QPSS in the transition phase; they may choose to continue using the QPSS if they wish but any data they provide will not be used in the study. Eighteen to twenty-four of the RCT participants will be interviewed about their experiences using the QPSS during this stage. The interviewees will be purposively sampled from the intervention arm, to achieve diversity in gender, age, health condition, and family caregivers' relationship (e.g., spouse, child, or friend).

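### The attrition margin in the sample size justification is counted on three groups, but Aim 1 is tested on the two randomised arms, where at the smaller effect almost none of it remains

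*Protocol*

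**What the plan says.** Section 6.9.2.1 describes the target effect in words, as "equivalent to changing an average day into a good day for patients (based on the MQOL" instrument), and continues: "Our power analysis has shown that sample sizes of 432 and 158 would be needed to detect small to moderate effect sizes". It does not say whether these are totals or group sizes. It then states: "We propose a larger sample of 540 (180 for each group) for both patients and family caregivers to account for attrition". The three groups are named there as pre-intervention, control and intervention.

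The trial itself is smaller. Section 6.1.2 tests the Aim 1 hypotheses in a two-arm parallel RCT, and for it, section 6.4.2.5 says "we will recruit a total of 360 patients and 360 family caregivers across all sites". The primary method in section 6.9.2 is analysis of covariance to "compare AUC scores of both outcomes (QOL and health care experience) across the intervention and control groups", and "All tests will be two-tailed with an alpha level of 0.05". The Stage 1 group is there to try out procedures and to explore contamination and system change (6.1.2, 6.2.2, 6.3.6). Beyond that it enters only the supplementary three-group growth models.

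**The concern.** The only justification of the trial's size measures its reserve for attrition on 540 people, a third of whom are neither randomised nor part of the primary comparison. If the required figures were worked out for three groups as well, they answer a different question from the one Aim 1 asks.

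Attrition matters in this trial. Participants have advancing life-limiting illness, and follow-up lasts 12 months or until discharge from home care or death (6.3.8). Some randomised patients may give no outcome data at all, because "consenting patients will be randomized (whether or not they intend to provide outcome data"). A reader of a null result could credit the trial with a reserve that has not been shown for its primary comparison.

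**Working it through.** **Inputs from the protocol.** Two-sided alpha 0.05; stated needs 432 and 158; 540 = 3 × 180; RCT of 360, allocated 1:1.

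**Inputs assumed, because the protocol does not give them.** 80% power; Cohen's f = 0.15 and 0.25; a one-way F test.

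**Step 1: reproduce the stated figures.** For k groups and total N, the noncentrality is λ = N·f², with k − 1 and N − k degrees of freedom. With k = 3:

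| f | N | Power |
|---|---|---|
| 0.15 | 431 | 0.7998 |
| 0.15 | 432 | 0.8008 |
| 0.25 | 157 | 0.7995 |
| 0.25 | 158 | 0.8022 |

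Both figures are the smallest totals that reach 80%. A search over 2, 3, 4 and 6 groups, four power levels and a range of f found no two-group test giving both at conventional effect sizes and a single power level.

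**Step 2: the implied attrition allowance.** 1 − 432/540 = 20%.

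**Step 3: the same f in two arms.** With two equal groups d = 2f, so f = 0.15 is d = 0.30 and f = 0.25 is d = 0.50. At 80% power the F test needs 351 and 128 in total (352 at d = 0.30 if the arms are kept equal). The margin at d = 0.30 is 1 − 351/360 = 2.5%. To keep a 20% allowance at that effect without covariate adjustment would take 351/0.8 ≈ 439.

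**Step 4: unadjusted two-arm power by loss from 360.**

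| Loss | Analysed | d = 0.30 | d = 0.50 |
|---|---|---|---|
| 0% | 360 | 81% | >99% |
| 10% | 324 | 77% | 99% |
| 20% | 288 | 72% | 99% |
| 30% | 252 | 66% | 98% |

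With 288 analysed, the difference detectable at 80% power is d ≈ 0.33.

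**Step 5: baseline adjustment.** If the baseline score correlates r with the outcome, the effective difference is d/√(1 − r²). With r = 0.5 (assumed), 0.30/√0.75 = 0.346, and power is 91% at 360 and 83% at 288. At 288, r of about 0.43 is enough to bring power back to 80%.

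**Step 6: how a three-group f translates into the intervention-control gap.** Step 3 carries f over unchanged. If f = 0.15 instead describes the spread of three means, the gap depends on their pattern:

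- Only the intervention group differs: d = 0.15 × 3/√2 = 0.318. The need is 313, the margin 1 − 313/360 = 13%, and power 77% at 288.
- Equally spaced, Stage 1 group in the middle: d = 0.15 × √6 = 0.367, and power is 87% at 288.
- Equally spaced, control in the middle: d = 0.367/2 = 0.184, and power is 41% even with all 360.

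**Step 7: other readings of 432.** As a two-arm total at 80% power it corresponds to d ≈ 0.27, and 360 is below it before anyone is lost. Read as a per-arm figure, the shortfall is larger.

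**The case against.** Four points on the other side have weight.

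- **The origin of the figures is inferred.** The protocol names no test, power or effect size. That is so, although two exact matches on conventional inputs make a strong inference. The mismatch does not depend on it: the comparison with the three-group 540 is the protocol's own.
- **The planned effect is a range.** At the moderate end, 128 are needed and power stays near 99% after 20% loss. This stands. The thin margin applies to the smaller effect, which is the one that produces 432.
- **The primary method is analysis of covariance, and baseline data are collected before randomisation (6.6.2.1).** Adjustment could restore 80% power at d = 0.30. This stands as a possibility, but the protocol gives no correlation and does not name baseline as the covariate, so neither 72% nor 83% is established.
- **Loss to follow-up need not remove a participant.** The outcome is an area under the curve over up to six administrations, and partial follow-up may still contribute. The losses in step 4 are therefore illustrations.

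A reader might go further and infer that the RCT falls short simply because 360 is less than 432. On the three-group reading that comparison is invalid: 432 spans three groups, and the two-arm need of 351 is met. It holds only if 432 was meant for two arms. A reader might also take the 41% in step 6 as the trial's power, but that follows only if control lies midway, and another ordering gives 87% after 20% loss.

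**Conclusion.** The justification is wrong as written: its reserve for attrition is counted on people outside the primary comparison. On the inferred inputs (f = 0.15, 80% power, no covariate adjustment), the two-arm margin is about 2.5% where 20% is implied, and power at 20% loss is 72%. Depending on how the three-group effect translates to two arms, the margin could be about 13%, larger, or absent. If 432 was a two-arm total, there is none.

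The documents do not support the stronger conclusion that the trial is underpowered. At d = 0.50 it is ample, and at d = 0.30 a moderate baseline correlation would make up the loss. What is missing is a calculation for the comparison actually tested.

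**What to change.** Rewrite section 6.9.2.1 as an intervention-versus-control calculation for 180 per arm, leaving the Stage 1 group out of the power statement. State:

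- the test and the target effect as a number;
- the attrition rate assumed (540 against 432 implies 20%);
- any baseline correlation relied on, with its source;
- the resulting power, or the detectable difference, after attrition;
- the number expected to provide outcome data, separately for patients and for caregivers. Some randomised patients may provide none, and the caregiver target of 360 equals the patient target with at most one caregiver per patient (6.4.2.1).

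The sponsor should take the effect and power from its own power analysis; the figures above rest on inferred inputs and should not be copied in. If the Stage 1 group needs a size justification for the contamination comparison, give it separately.

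The cost is protocol wording. No extra enrolment is needed, but the stated margin becomes less favourable.

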## 6.9.3 Analysis of administrative data in cost-effectiveness evaluation

The primary economic evaluation work will involve the comparison of data from stages 1 and 2; the cost-effectiveness evaluation will focus on Stage 2 of the project, running in parallel with, and drawing data from, other components. The framework for the economic analysis will be cost-consequence analysis, where the costs and outcomes of the alternatives are listed separately in a disaggregated format (e.g., intervention costs, hospital costs, clinical benefits, and QOL). As a complement to the cost-consequence analysis, a cost-utility approach will also be employed, with outcomes expressed as quality-adjusted life years (QALYs). The time horizon will be 12 months (consistent with outcomes), and a broad perspective will be adopted to consider both health sector and participant/family costs.

Using health administrative data for each participant, we will determine: (a) frequency and length of use of the QPSS of the home care team, including the number of home care visits and consultations with interdisciplinary team members; and (b) use of other health services, including emergency and acute care admissions. In addition, for the intervention group, the amount of clinician time to use the QPSS and other implementation costs will be captured by the Cambian Coordinator system). The dollar value of resources will be determined using local Fraser Health accounts data, supplemented using the Canadian Institutes of Health Information patient cost estimator for acute sector admissions ([www.cihi.ca](http://www.cihi.ca)).

Bootstrapping will be used for comparison of the mean costs and QALYs between groups, with non-parametric confidence intervals, and to estimate the incremental cost-utility ratio. The bootstrapped cost-effect pairs can graphically be represented on a cost-effectiveness plane, and cost-effectiveness acceptability curves calculated, showing the probability that an intervention is cost-effective at a specific threshold ratio. This information will be used to evaluate relative cost for each of the groups and ascertain whether QPSS implementation results in cost-saving or expense.

A data access request will be submitted to identify the specific data elements that will be used for the study.

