STAGE 1: The **local adaptation stage** will use qualitative methods (user-centered design focus groups and interviews with clinicians, managers, patients, and family caregivers) to adapt the QPSS to the unique context of each site and develop protocols for its routine integration in daily practice. To test the recruitment and data collection procedures and explore the possibility of contamination and the potential impact of changes in the health care system between Stages 1 and 2, this will also include (a) measurement of patient and family caregiver QOL and health care experiences prior to routine use of the QPSS in home care to serve as a pre-intervention comparator group (Aim 1) and (b) data collection regarding the cost of local adaptation and training (Aim 2).

TRANSITION PHASE: In the last 6 months of Stage 1, a few clinicians from each site will explore the use of the QPSS with 1 to 2 of the clients in their respective caseload. The clinicians trying out the QPSS will provide feedback on their experience using the system via focus group (in Stage 1) and through one-time individual interview. Clients and family caregivers who tried out the QPSS will also be interviewed. The feedback from clinicians, clients and family caregivers will inform the development of the site protocol, as well as the preparation for QPSS implementation in Stage 2.

STAGE 2: During the **evaluation stage**, we will (a) conduct a randomized controlled trial (RCT) to evaluate the impact of using the QPSS on the QOL and care experiences of patients and their family caregivers (Aim 1); (b) conduct an economic evaluation to estimate the cost consequences of the QPSS in home care (Aim 2) in the last six months of Stage 2; and (c) apply qualitative and quantitative methods to examine the use of the QPSS in home health care (Aim 3).

STAGE 3: The **sustainability stage** will focus on (a) whether the results warrant sustained and widespread integration of the QPSS into practice, and if so, (b) how to scale this up, (c) how to further integrate the QPSS with other health information systems to facilitate use by health care administrators for continuous quality improvement and accreditation (Aim 4) and (d) dissemination of results.

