### 6.3.3 Control group

In the control group, patients and family caregivers will use the Navigator system independently of the clinicians. Clinicians *will not* use the Coordinator system with this group of patients, nor will the data collected from the control group be made available to clinicians. Clinicians will not know the identity of the patients and family caregivers in the control group, and this group of patients and family caregivers will continue to receive care as usual from their clinicians.

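### Section 6.9.3 labels a non-randomised Stage 1 versus Stage 2 comparison as the primary economic work and does not reconcile it with the randomised contrast available in Stage 2

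*Protocol*

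**What the plan says.** Section 6.9.3 opens with "The primary economic evaluation work will involve the comparison of data from stages 1 and 2". The second half of the same sentence reads "the cost-effectiveness evaluation will focus on Stage 2 of the project". The section then sets the method: "The framework for the economic analysis will be cost-consequence analysis", with a cost-utility analysis as a complement. On inference it says "Bootstrapping will be used for comparison of the mean costs and QALYs between groups", and it does not say which groups. From that material it intends to conclude whether implementation saves money or adds expense. On the window: "The time horizon will be 12 months (consistent with outcomes").

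Elsewhere, Sections 6.1.2 and 6.3.4 describe Stage 2 as a two-arm parallel trial randomised 1:1 and stratified by site. Of the control arm, Section 6.3.3 says "this group of patients and family caregivers will continue to receive care as usual from their clinicians". Sections 6.1.2 and 6.2.2 give the Stage 1 outcome group an exploratory purpose: to look for contamination and for the effect of health-system change between the stages. Section 6.4.2.5 adds: "The RCT participants may include Stage 1 participants". The summary in Section 2 says that in Stage 2 the team will "conduct an economic evaluation to estimate the cost consequences of the QPSS in home care (Aim 2) in the last six months of Stage 2".

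**The concern.** The trial has a concurrent randomised usual-care arm, and Section 6.9.2 uses it for the clinical outcomes. For costs, the comparison called primary is between stages. Stage 1 participants are not randomised against anyone in Stage 2 and are observed in an earlier calendar period. Any change in service provision, prices or referral practice between the stages would be counted as an effect of the QPSS. The protocol recognises this kind of change, since exploring it is one of its reasons for collecting Stage 1 data. People may also take part in both stages, so the two samples may not be independent.

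At stake is the answer to Aim 2. If the stage contrast carries the conclusion, a finding of saving or expense could reflect the calendar. If the randomised contrast is meant to carry it, the text does not say so.

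**Working it through.** **Plan's own figures.** The protocol gives no economic sample size or power. Its only power figures, 432 and 158 in Section 6.9.2.1, match a three-group one-way ANOVA at alpha 0.05 if 80% power and Cohen's f of 0.15 and 0.25 are assumed. They do not bear on which economic contrast is primary. Only the group size of 180 is used below.

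**What each contrast estimates.** Let *e* be the true cost effect and *d* the change in mean cost between stages that would have happened anyway, both in standard deviations.

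- Stage 2 intervention minus Stage 1: *e* + *d*.
- Both Stage 2 arms pooled minus Stage 1: (180/360)*e* + *d* = 0.5*e* + *d*.
- Stage 2 intervention minus Stage 2 control: *e*. A change common to both arms cancels.

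Section 6.9.3 does not say whether Stage 2 in the first clause means the intervention arm or both arms, so both readings are shown.

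**Illustration.** Assumptions: *e* = 0, independent groups, normal approximation, two-sided alpha 0.05 (Section 6.9.2), no attrition. The drift values are assumed; the documents give none. The rejection probability is Φ(d/SE − 1.96) + Φ(−d/SE − 1.96).

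- Stage 1 (180) vs Stage 2 intervention (180): SE = √(2/180) = 0.1054.
- Stage 1 (180) vs both Stage 2 arms (360): SE = √(1/180 + 1/360) = 0.0913.

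| Assumed drift (SD) | Stage 1 vs intervention | Stage 1 vs pooled Stage 2 | Randomised contrast |
|---|---|---|---|
| 0 | 5.0% | 5.0% | 5.0% |
| 0.1 | 15.8% | 19.5% | 5.0% |
| 0.2 | 47.5% | 59.1% | 5.0% |
| 0.3 | 81.2% | 90.8% | 5.0% |

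Under pooling, a true effect is also halved. With *e* = 0.3 and no drift, power is Φ(0.3/0.1054 − 1.96) = 81% for the randomised 180 vs 180, and Φ(0.15/0.0913 − 1.96) = 38% for Stage 1 vs pooled Stage 2.

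**Calendar gap.** Section 6.4.1.5 puts the earliest Stage 2 start at 1 November 2017. Section 8 dates the Fraser Health offices' enrolment to February 2016, July/August 2016 and December 2016. The gaps to the earliest start are about 21, 15 to 16 and 11 months. These are office enrolment dates, not participants' cost windows, and Edmonton has no exact date.

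**Sample size after the change.** Intervention versus control is 180 vs 180, the same as Stage 1 versus intervention. Nothing is lost relative to that reading.

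**The case against.** The strongest reply is that the first clause should not be read alone. The second clause turns the cost-effectiveness evaluation to Stage 2, and the rest of Section 6.9.3 uses the language of arms: alternatives, the intervention group, comparison between groups. The conclusion about saving or expense follows the bootstrap paragraph, not the stage sentence. This stands in part. A reader might infer that the plan discards the randomised control arm for costs. The text does not support that, because a randomised economic comparison may well be intended. It still calls the stage comparison primary and never says which groups the bootstrap compares.

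Sections 2 and 6.1 defer economic detail to a later amendment. That makes the correction easy, but Section 6.9.3 already fixes a primary comparison, so this is a stated choice and not a detail left open.

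Clinicians care for both arms, and Section 6.3.6 makes no effort to prevent contamination, so the randomised cost contrast may be attenuated. This is a fair reason to keep a Stage 1 comparison in a supporting role. The protocol does not offer it as a reason for making that comparison primary.

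The two windows need not conflict. The last six months of Stage 2 in Section 2 may describe when the work is done, and 12 months the costing horizon. A reader might infer that only half the horizon will be observed, but the documents do not establish that. What remains is a scheduling ambiguity, since Sections 6.3.9 and 6.9.3 say the evaluation runs in parallel with the other components.

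**Conclusion.** The point holds as an unreconciled specification in which the contrast labelled primary is the non-randomised one, exposed to a calendar change that the protocol itself anticipates. No reason is given for preferring it to the randomised contrast.

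The size depends on drift that the documents do not quantify. At an assumed 0.2 SD, the false-positive rate is about 48% against the intervention arm and 59% against pooled Stage 2, compared with 5% for the randomised contrast. Costs are usually skewed and some participants may be in both stages, so these figures show direction and order of magnitude only.

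Three stronger readings go beyond the text:

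- Halving of the effect applies only if both Stage 2 arms are pooled, which is not stated. Section 6.9.2.1 defines three separate groups.
- A 21-month gap fits only the first two offices. The range to the earliest Stage 2 start is about 11 to 21 months across the offices with stated dates.
- Being a year or more further into illness is nowhere stated. It could concern only people in both stages, a subset of unknown size.

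The randomised analysis of the clinical outcomes is unaffected. The consequence is confined to Aim 2.

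**What to change.** In Section 6.9.3, state that the primary cost-consequence and cost-utility comparison, including the bootstrap of costs and QALYs, is intervention versus control as randomised in Stage 2 over the 12-month horizon. Keep Stage 1 as the source of adaptation and training costs, and as a supportive comparison for contamination and secular change. For that supportive comparison, name the Stage 2 arm or arms used and say how people who are in both stages are handled. In Section 2, say whether the last six months of Stage 2 is when the economic work is carried out or the period over which costs are counted.

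The cost is wording, which fits the economic amendment already planned and is best settled before the data access request is submitted. No additional participants are needed. The drawback is that contamination through shared clinicians may attenuate the randomised cost difference; the supportive Stage 1 comparison can help explore this but cannot remove it.
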